|---------------------------------------------------------------------------|------------------|-------------|------------------|---------|---------|---------------------|---------------------|----------------------------------------------------|---------------------|
| Visit                                                                     | V1               | V2          | V3               | V4      | V5      | V6 & | V7 & | V8 ▲                                    | V9/EOS ▲ |
| Planned visit date                                                        | D-7~D0           | D0          | D7               | D14     | D28     | D90                 | D180                | After the final efficacy analysis                  | D365                |
| Visit window period                                                       | /                | /           | +2 days          | ±3 days | +7 days | ±10 days            | ±10 days            | /                                                  | ±10 days            |
| efficacy follow-up may be adjusted according to the process of the study. |                  |             |                  |         |         |                     |                     |                                                    |                     |
| Safety follow-up visit                                                    |                  |             |                  |         |         |                     |                     |                                                    |                     |
| Solicited AEs                                                |                  | ●           |                  |         |         |                     |                     |                                                    |                     |
| Unsolicited AEs                                              |                  | ●           |                  |         |         |                     |                     |                                                    |                     |
| SAEs and AESIs                                               |                  | ●           | ●                | ●       | ●       | ● #      | ● #      | ● #                                     | ● #      |
| Observing for at least 30 minutes after the vaccination                   |                  | ●           |                  |         |         |                     |                     |                                                    |                     |
| Distributing the vaccination record cards (VRCs)                          |                  | ●           |                  |         |         |                     |                     |                                                    |                     |
| Reviewing and recovering the VRCs                                         |                  |             |                  | ●       | ●       |                     |                     |                                                    |                     |
| Distributing the thermometer and tape measure                             |                  | ●           |                  |         |         |                     |                     |                                                    |                     |
| Recording the concomitant medication                                      |                  | ●           | ●                | ●       | ●       | ● #      | ● #      | ● #                                     | ● #      |

Abbreviations: AE=Adverse Event, AESI=Adverse Event of Special Interest, SAE=Serious Adverse Event, VRC=Vaccination Record Card

Comments:

&: V6 and V7 are only applicable for participants in the immunogenicity subgroup.

▲: For V8 and V9, this visit will be done by phone call or other means of telecommunication, while it can also be done on-site if necessary, if the participants received other marketed COVID-19 vaccines, the participants should withdraw from the study.

★: If screening and vaccination are on the same day (D0), there is no need to repeat the items corresponding to ‘●★’ before vaccination.

#: 28 days after each study vaccination, only the concomitant medication used to treat SAEs and AESIs should be recorded.

\*: Participants are randomized after all the tests have been done and eligibility has been confirmed before the vaccination on the vaccination day.

1. Inclusion/exclusion criteria should be reviewed during the screening period and before vaccination on the day of vaccination.
2. Demographic data: including date of birth, sex, race/ethnicity, height, body weight, and BMI (derived from height and body weight). The participants should also provide contact information like their current phone number and/or E-mail. In subsequent follow-up visits, if the contact information is changed, it should be updated accordingly (if applicable).
3. Records of medical history: including the history of SARS-CoV-2 vaccination, history of COVID-19, other vaccinations within 28 days, medication use within 28 days, major surgery, allergic history and other known significant diseases.
4. Nasal/pharyngeal/throat swab for rapid antigen test and nucleic acid test for SARS-CoV-2: A rapid antigen test or nucleic acid test should be performed at screening at the study site before vaccination. Participants with positive results will be excluded from the study. Nasal/pharyngeal/throat swab samples for nucleic acid test should be collected from all participants before vaccination and there is no need to wait for the report for vaccination. If screening vaccination is on the same day, there is no need for repeat nucleic acid tests. Before the participants signed the ICF, if the participants have been sampled for rapid antigen test or nucleic acid test during the screening period, there is no need for repeat test (determined by the investigators).
5. Vital signs: blood pressure, respiratory rate, pulse rate, and body temperature.
6. Physical examinations: general conditions, head & neck, lymph node, skin, chest, abdomen, musculoskeletal system and other examinations necessary for the study.
7. Anti-SARS-CoV-2 IgG antibodies: The baseline SARS-CoV-2 anti-Spike IgG will be measured during the screening period, participants will be excluded from the study if the baseline SARS-CoV-2 anti-Spike IgG is higher than the upper limit (in regions with low incidence of SARS-CoV-2 infection, this criteria may be adjusted or not be applied, if the number of participants exceeding this threshold reaches a certain proportion, the participants will be restricted to enroll according to this upper limit, on the contrary, the participants will be sampled during screening period without waiting for the result before enrollment). If the upper limit of baseline SARS-CoV-2 anti-Spike IgG >338BAU/mL was not the excluding criteria, the blood sample should be collected before the vaccination;
8. Urine pregnancy test (for women of childbearing potential only): the urine pregnancy test may be performed routinely, while the blood pregnancy test may be performed if the investigator deems it necessary. A woman is considered of childbearing potential (WOCBP), i.e. fertile, following menarche and until becoming post-menopausal unless permanently sterile. Permanent sterilization methods include hysterectomy, bilateral salpingectomy and bilateral oophorectomy. A postmenopausal state is defined as no menses for 12 months without an alternative medical cause.
9. For Participants who request to be unblinded and are confirmed to be placebo recipients, the following procedure is available: 1) remain in the study for continued follow-up; 2) withdraw from the study by vaccination with other marketed vaccines; 3) withdraw from the study for other reasons. All participants will be encouraged to remain in the

---

ongoing study until the end of the study, unless they request to withdraw from the study for any reason.

10. Neutralizing antibodies test: participants in the immunogenicity subgroup (5%-10% of the population in FAS) will be sampled on Days 0 (before vaccination), 14, 28. 200 participants in the immunogenicity subgroup will be sampled on Days 7, 90, 180 and 365 for nAb of SARS-CoV-2 (including variants and subvariants).
11. Solicited and unsolicited AEs: collect solicited AEs from D0 to D7, and unsolicited AEs from D0 to D28.

SAEs, and AESIs: SAEs, and AESIs will be collected on visit day or reported by participants actively at any time. If participants cannot come to the site on visit day, phone calls, short messages, email or other contacting methods will be used for safety follow-up.

**A Randomized, Double-blind, Placebo-controlled Phase III  
Clinical Trial to Evaluate the Efficacy and Safety of SCTV01E  
(A COVID-19 Alpha/Beta/Delta/Omicron Variants S-Trimer  
Vaccine) in Healthy Adults Aged  $\geq 18$  Years**

Sponsor: Sinocelltech Ltd.

Study facilities: Guizhou Center for Disease Control and  
Prevention

Sichuan Center for Disease Control and  
Prevention

Hunan Provincial Center for Disease  
Control and Prevention

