**Efficacy follow-up:**

Follow-up of protective efficacy will be started after the study vaccination. All participants will be asked whether they have any signs/symptoms related to COVID-19 by phone call, short message, email or other contacting methods once a week. The frequency of the efficacy follow-up may be adjusted according to the process of the study. Meanwhile, the participants could spontaneously report any COVID-19-related symptoms at any time during the study period. SARS-CoV-2 RT-PCR test will be performed if participants have signs/symptoms related to COVID-19. If participants meet the criteria for symptomatic infection of SARS-CoV-2 for the primary study endpoint, the virus will be isolated from the nasal/nasopharyngeal/throat swab and viral sequencing will be performed to identify the SARS-CoV-2 variants. Endpoint Adjudication Committee (EAC) will be set up in this phase III study to conduct independent evaluation and judgment for each case, to ensure a more accurate determination of the positive cases.

**Immunogenicity follow-up:** Participants in the immunogenicity subgroup will be sampled on Days 0 (before study vaccination), 14, and 28. 200 participants in the immunogenicity subgroup will be sampled on Days 7, 90, 180 and 365 for nAb of SARS-CoV-2 (including variants and subvariants).

**Safety follow-up:** All participants will be observed at site for at least 30 minutes after the study intervention. Both active monitoring and spontaneous reporting will be used. Solicited AEs within 7 days after the study vaccination and unsolicited AEs within 28 days after the study vaccination will be collected through vaccination record cards (VRCs).

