|                                            | 
SAEs and AESIs will be actively monitored for about 365 days after the study vaccination.
 
IDMC: An Independent Data Monitoring Committee (IDMC) will be set up to review the safety data after the study vaccination,
 
Participants can choose whether to be blinded or not after obtaining statistically significant vaccine efficacy and adequate safety data. Participants will be encouraged to remain in the ongoing study until the end of the study, unless they request to withdraw from the study for any reason. SAEs and AESIs would be monitored during this time.
 
For participants who request to be unblinded and are confirmed to be placebo recipients, the following procedure is available:
 
 
1) remain in the study for continued follow-up;
 
2) withdraw from the study by vaccination with other marketed vaccines;
 
3) withdraw from the study for other reasons.
 
 
Participants who receive or request any other COVID-19 vaccination during the study should withdraw from the study.
 |
| 
Total Number of Participants
 | 
Approximately 10,000 participants are planned to be enrolled. The percentage of participants aged <math>\geq 60</math> years shouldn't be less than 20%, and the percentage of participants who have received 3 doses of inactive COVID-19 vaccines shouldn't be less than 60%. The exact number of participants enrolled in the study will depend on the infection rate of COVID-19 at the time of the enrollment and the true VE (vaccine efficacy) of SCTV01E. If the attack rate is much higher, case accrual would be expected to be more rapid, enabling the study's primary endpoint to be evaluated much sooner and the actual enrolled sample size may be less than planned.
                                                                                                                                                                                                                                                                                                                                                                                                                         |

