**Immunogenicity evaluation:** Blood samples will be collected on Day 0 (pre-vaccination), Day 14 and Day 28 from participants in the immunogenicity subgroup (approximately 5%–10% of randomized participants), of which 200 participants need to undergo additional scheduled sampling on Day 7, Day 90 and other longer periods (detailed in the visit flow chart of the protocol) for the detection of SARS-CoV-2 (including mutant strains and mutant subtype) neutralizing antibody.

**Safety evaluation:** All participants will be observed at the study site for at least 30 minutes after the study intervention. Information is collected through a combination of active surveillance and spontaneous reporting. Solicited adverse events (AEs) within 7 days after vaccination and unsolicited AEs within 28 days after vaccination will be collected via vaccination record cards (VRCs). Serious adverse events (SAEs) and adverse events of special interest (AESIs) will be collected through active surveillance until the participant completes (or withdraws early from) the study.

This study will be conducted by Guizhou Center for Disease Control and Prevention, Sichuan Center for Disease Control and Prevention, and Hunan Provincial Center for Disease Control and Prevention.

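### Active SAE/AESI monitoring for about 365 days is stated for all participants, but the schedule gives 90–95% of them no fixed-day SAE/AESI contact between Day 28 and Day 365

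*Combined protocol and SAP*

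**What the plan says.** The Safety follow-up part of the protocol synopsis states: "SAEs and AESIs will be actively monitored for about 365 days after the study vaccination". SAP section 4.1 (Safety evaluation) says that SAEs and AESIs "will be collected through active surveillance until the participant completes (or withdraws early from) the study". Neither limits this to a subgroup. The synopsis lists the incidence and severity of SAEs and AESIs among the secondary safety endpoints.

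Table 1 (Schedule of Activities) marks SAE/AESI collection at V2 to V5 (Day 0 to Day 28), V6 (Day 90), V7 (Day 180), V8 and V9 (Day 365). Footnote & reads: "V6 and V7 are only applicable for participants in the immunogenicity subgroup". The final Table 1 comment describes the mode of collection: "SAEs, and AESIs will be collected on visit day or reported by participants actively at any time". Footnote 10 gives the size of the subgroup: "participants in the immunogenicity subgroup (5%-10% of the population in FAS) will be sampled on Days 0 (before vaccination), 14, 28". It adds: "200 participants in the immunogenicity subgroup will be sampled on Days 7, 90, 180 and 365 for nAb of SARS-CoV-2".

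V8 is placed after the final efficacy analysis, with no study day and no visit window. It is open to all participants, and footnote ▲ lets V8 and V9 be done remotely.

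There is also a weekly efficacy contact: "All participants will be asked whether they have any signs/symptoms related to COVID-19 by phone call". The same paragraph adds: "The frequency of the efficacy follow-up may be adjusted according to the process of the study".

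**The concern.** Footnote & restricts the whole of V6 and V7, not only the blood draw. With SAE/AESI collection tied to visit days or to the participant's own initiative, someone outside the subgroup has no safety contact on a set day for about eleven months. That is hard to reconcile with active surveillance. What is at stake is the completeness and timeliness of late SAE and AESI data, and so how firmly a low late count can be read as evidence of longer-term safety.

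**Working it through.** There is no stated figure to reproduce. The check sets the schedule against the stated monitoring and sizes the difference.

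**Participants affected**
- Inputs: 10,000 planned (synopsis); subgroup 5–10% (Table 1, footnote 10); FAS of 9,196 (Table S1).
- Outside the subgroup, planned: 10,000 × 0.90 = 9,000 to 10,000 × 0.95 = 9,500.
- Outside the subgroup, FAS: 9,196 × 0.90 ≈ 8,276 to 9,196 × 0.95 ≈ 8,736.
- If Day 90 and Day 180 are in practice attended only by the 200 who are sampled then: 10,000 − 200 = 9,800, or 98.0%. Footnotes & and 10 leave open which of the two applies.

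**Length of the interval**
- Nominal: 365 − 28 = 337 days.
- With the Table 1 windows (Day 28 +7, Day 365 ±10): from 355 − 35 = 320 to 375 − 28 = 347 days.
- For participants who do attend V6 and V7, the same period splits into 90 − 28 = 62, 180 − 90 = 90 and 365 − 180 = 185 days.

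**What else might fill the interval outside the subgroup**
- V8 collects SAEs and AESIs from everyone, but its timing depends on case accrual (at least 59 primary events) and on completion of the analysis. No participant-level day is assured.
- The weekly contact would give about 337 / 7 ≈ 48 contacts at the stated frequency. Its stated content is COVID-19 symptoms, Table 1 lists it under efficacy follow-up and apart from safety follow-up, and its frequency is adjustable. SAP section 4.1 gives no weekly interval.
- The final Table 1 comment offers phone, message or email when a participant cannot attend on a visit day. That changes the mode of a scheduled visit and adds no further contact.

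So V8 (undated), V9 (Day 365) and participant reports are all that is specified for SAE/AESI collection after Day 28 in most of the trial.

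**The case against.** The strongest reply is that these participants are not out of touch. Staff contact everyone weekly, and a hospitalisation would often come to light. Table 1 calls the weekly contact a follow-up visit, so one could argue that it counts as a visit day for SAE collection, and nothing says that SAE questions are excluded. In part this stands: the weekly contact would probably reveal some serious events. But its stated content is limited to COVID-19 symptoms and safety follow-up is listed separately, so the visit-day reading is strained. Incidental discovery is not specified ascertainment.

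V8 also may not be late. On the sample-size assumptions (1.5% per month in controls, VE 70%, losses of 15% and 10%), 10,000 × 0.85 × 0.90 = 7,650, or 3,825 per arm. Monthly cases are then 3,825 × 0.015 + 3,825 × 0.0045 ≈ 75, and 59 / 75 ≈ 0.8 months. With the PPE of Table S2, 1,309 × 0.015 + 1,314 × 0.0045 ≈ 25.5 per month, and 59 / 25.5 ≈ 2.3 months. Staggered enrolment and analysis time come on top and are not given. This stands. A reader might infer that most participants get a single recall call at the end, or that the IDMC sees no actively collected data after Day 28. V8 contradicts the first, and the second is unsupported, since V8 could fall within the first months and the IDMC charter is not supplied.

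A reader might also extrapolate from Table S6: 37 participants had SAEs within 28 days, and 37 / 28 × 337 ≈ 445, against 41 recorded later. That does not show under-reporting. It assumes a constant rate over a full year, and the data cut-off for Table S6 is not given. What Table S6 does show is that late SAEs were captured by some route: 41 of 78 participants with SAEs (53%), 21 on placebo and 20 on SCTV01E.

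Finally, the protocol body is not in the supplied document. The synopsis and Table 1 refer to Sections 9.3.4 and 11.4.4, which are absent, and safety procedures may be described in the body.

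**Conclusion.** The mismatch holds and should be fixed. As written, the schedule does not specify the active surveillance that the synopsis and SAP section 4.1 state. For 90–95% of participants (9,000–9,500 of 10,000) there is no SAE/AESI contact with a fixed study day for a nominal 337 days; the share is 98% if only the 200 persistence participants attend V6 and V7.

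The consequence is a risk: late SAEs and AESIs may be captured less completely or later in most participants. The same schedule applies to both arms, so the expected loss is in sensitivity; no bias between arms is demonstrated, and neither is actual under-reporting.

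The conclusion assumes that the weekly contact carries no SAE/AESI question, which the documents supplied do not state either way, and that the protocol body adds no further safety contact.

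**What to change.** Reconcile the Safety follow-up text in the synopsis, the efficacy and safety rows and comments of Table 1, and SAP section 4.1:
- Limit footnote & to the blood sampling at V6 and V7, and state whether the whole subgroup or only the 200 are sampled there.
- Add one fixed SAE/AESI question, such as hospital admission or new serious illness, to the remote contact already made with every participant.
- If the weekly frequency is reduced, keep that contact for everyone at least around Day 90 and Day 180.

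If the protocol body already provides for this, a cross-reference in Table 1 and the SAP is enough. The cost is a footnote amendment, slightly longer contacts and some extra data entry. No new sample or procedure is needed.

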## 1. Description of Abbreviations and Statistics (in English) Used

|          |                                              |
|----------|----------------------------------------------|
| AE       | Adverse Event                                |
| AESI     | Adverse Event of Special Interest            |
| COVID-19 | Coronavirus Disease 2019                     |
| EAC      | Endpoint Assessment/Adjudication Committee   |
| FAS      | Full Analysis Set                            |
| IDMC     | Independent Data Monitoring Committee        |
| I-FAS    | Full Analysis Set for Immunogenicity         |
| I-PPS    | Per-Protocol Set for Immunogenicity          |
| IPS      | Immunogenicity Persistence Set               |
| ITT      | Intention to Treat                           |
| IWRS     | Interactive Web Response System              |
| LLOQ     | Lower Limit Of Quantitation                  |
| LOCF     | Last Observation Carried Forward             |
| Max      | Max                                          |
| Mean     | Mean                                         |
| MedDRA   | Medical Dictionary for Regulatory Activities |
| Median   | Median                                       |
| Min      | Min                                          |
| PPE      | Per-Protocol Set for Efficacy                |
| PPS      | Per-Protocol Set                             |
| PCR      | Polymerase Chain Reaction                    |
| PT       | Preferred Term                               |
| SAE      | Serious Adverse Event                        |
| SAP      | Statistical Analysis Plan                    |
| SAS      | Statistical Analysis System                  |
| SD       | Standard Deviation                           |
| SOC      | System Organ Class                           |
| SS       | Safety Set                                   |
| TEAE     | Treatment Emergent Adverse Event             |
| WHO DD   | World Health Organization Drug Dictionary    |

